### The treatment of cardiovascular risk in primary care using electronic decision support (TORPEDO) study

There have been few randomised evaluations of QI interventions in the Australian primary healthcare setting. We designed a multifaceted QI intervention for CVD risk management in Australian primary healthcare. The intervention drew on two established QI mechanisms: 1) electronic decision support and 2) audit and feedback (summary of the clinical performance over a specified period of time) [32-37]. The intervention was evaluated in the TORPEDO study, a cluster-randomised controlled trial (cRCT) involving 60 health services. Details of the trial are published elsewhere [38]. In brief, the system was integrated with the healthcare provider’s EHRs, and included (1) a real-time decision support interface using an algorithm derived from several evidence based national guidelines (Figure 1); (2) a patient risk communication interface which included ‘what if scenarios’ to show the benefits from particular health risk factor improvement during a consultation (Figure 2); (3) an automated clinical audit tool for extraction of data and review of health service performance (Figure 3); and (4) a web portal where services can view peer-ranked performance over time (Figure 4). Healthcare providers could use the point-of-care tool as part of a routine clinical consultation. For the audit and feedback component, quality indicators were developed for patients who had visited the health service at least three times in the preceding 2 years and once in the preceding 6 months. The population studied was based on national guideline recommendations for CVD risk screening and included Aboriginal and Torres Strait Islander people over 35 years and all others over 45 years [38].

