**Quality improvement portal.**

Data were collected for 38,725 people from the 60 health services. Overall, when compared with control, the intervention was associated with a 25% relative (10% absolute) improvement in CVD risk factor screening. Overall, there was no significant difference in the prescribing rates of recommended medicines to people at high CVD risk. The intervention was, however, strongly associated with improvements in the sub-group at high CVD risk that was not prescribed with recommended medicines at baseline. There were also improvements in intensification of existing, recommended medication regimens. There were modest improvements in attaining blood pressure targets but no differences in other clinical outcomes. The improvements in recommended prescriptions to high risk patients were not accompanied by increased prescribing rates for patients at low risk [39].

Although the intervention exhibited significant improvements in some outcomes, it remains unclear how this intervention was actually used in practice and what factors promoted and hindered its use. Answers to these questions are critical in order to inform future directions for its implementation and for implementation of similar interventions in other settings.

In this paper, we outline our protocol for a theory-based process evaluation of the TORPEDO intervention. The broad objectives are to understand how, why, and for whom the intervention produced the observed outcomes and to develop effective strategies for translation and dissemination. The evaluation will identify which intervention components promoted or had minimal impact at the provider, patient, and system levels and the mechanism of change. It will also identify the contextual influences on the delivery of the intervention and its outcomes. The specific objectives are the following:To understand whether intervention effects are sustained in a post-trial setting;To identify implementation barriers and enablers;To understand how CVD risk is communicated in the doctor/patient interaction both with and without the use of the intervention; andTo identify cost considerations for delivering the intervention at scale in the Australian primary healthcare system.

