#### Analysis

Log-binomial regression will allow direct estimation of risks and risk ratios (i.e. relative risks) on each outcome. The model will be adjusted with intervention (yes vs. no) and time (baseline, 12 and 24 month) as categorical data where baseline is set as reference and interaction between intervention and time. The model will be adjusted with the intervention (yes or no) and with a random centre effect. Chi-square test and 95% confidence intervals (CI) will be computed.

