### Study 2: Multilevel modelling study (objective 2)

#### Aim

To determine what patient and health service level variables correlate with the trial outcomes.

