#### Methods

Patient variables (age, gender, ethnicity, history of CVD, and diabetes) will be obtained from the automated clinical audit tool, and health service level variables will be collected through Team Climate Inventory (TCI) and Warr-Cook-Wall job satisfaction surveys, customised for use with general practices (GPs) and Aboriginal Community Controlled Health Services (ACCHSs), administered to all general practitioners and other practice and health service staff at the participating 60 sites [56,57]. In addition, health service characteristics such as service size, participation in quality improvement programs, and type of primary healthcare (GP verses ACCHS) will be collected at randomisation.

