#### Analysis

TCI is a 44-item questionnaire, and items are rated on a 5-point scale [56]. Job satisfaction is a 15-item questionnaire, and items are rated on a 7-point scale [57]. Multilevel regression model analysis will be conducted to evaluate the influence of team climate and job satisfaction on the primary study outcomes, controlling for patient’s age, gender, practice size, type of PHC, and participation in quality improvement programs. The results will be interpreted within the context of the three conceptual perspectives to better understand what health service factors (if any) are important drivers of use of the intervention in routine practice.

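### Study 2 sets out to find patient-level correlates and collects five patient variables, but its one stated model leaves out ethnicity, CVD history and diabetes

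*Protocol article*

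**What the plan says.** All of this stands in the protocol article, under Study 2: Multilevel modelling study.

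- **Aim:** "To determine what patient and health service level variables correlate with the trial outcomes".
- **Methods, patient level:** "Patient variables (age, gender, ethnicity, history of CVD, and diabetes) will be obtained from the automated clinical audit tool".
- **Methods, service level:** staff surveys of team climate and job satisfaction, and in addition characteristics such as "service size, participation in quality improvement programs, and type of primary healthcare (GP verses ACCHS) will be collected at randomisation".
- **Analysis:** one multilevel regression is described. Its purpose is "to evaluate the influence of team climate and job satisfaction on the primary study outcomes", and it controls for the patient's "age, gender, practice size, type of PHC, and participation in quality improvement programs".

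The Analysis subsection gives ethnicity, history of CVD and diabetes no role, either as variables under study or as controls, and gives no reason for leaving them out.

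**The concern.** The aim has two halves, patient and service. The stated model serves the service half and gives the patient half only age and gender. An analyst who follows the text would report nothing on three of the patient variables that the study set out to obtain.

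The document itself shows why these three are not incidental:

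- **Ethnicity** fixes the age at which people entered the trial population, which "included Aboriginal and Torres Strait Islander people over 35 years and all others over 45 years".
- **History of CVD** separates secondary prevention from prevention guided by absolute risk, a distinction drawn in the Background under Evidence practice gaps. One of the two primary outcomes is prescribing to people at high risk.
- **Diabetes** is named in the Background among the modifiable causes of CVD.

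The Study 2 results are to be read as showing which service factors drive use of the intervention, and they feed the case studies in Study 3. If patient mix differs between services with good and poor team climate, part of that difference could be read as an effect of climate.

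**Working it through.** Study 2 states no sample size, power or effect estimate, so there is no figure to reproduce. The check has three parts.

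**1. Variables collected against variables modelled**

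| Variable | Collected (Methods) | In the stated model (Analysis) |
|---|---|---|
| Age | yes | yes |
| Gender | yes | yes |
| Ethnicity | yes | no |
| History of CVD | yes | no |
| Diabetes | yes | no |
| Service or practice size | yes | yes |
| Type of primary healthcare | yes | yes |
| QI participation | yes | yes |
| Team climate, job satisfaction | yes | yes (exposures) |

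Patient level: 2 of 5 carried through, 3 dropped. Named service characteristics: 3 of 3 carried through. The covariate list in the Analysis is closed. It has no wording such as *including*, whereas the Methods introduce the service characteristics as examples.

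**2. What the eligibility rule does to age without ethnicity**

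Under the stated age limits, anyone aged between 35 and 45 in the data is Aboriginal or Torres Strait Islander. Above 45 both groups are present. Age and ethnicity are therefore linked by design. In a model with age but no ethnicity term, the age coefficient takes up part of any ethnicity difference, and so may type of service (GP or ACCHS).

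**3. Possible size of bias in the climate and satisfaction estimates**

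On a linear scale, the bias from one omitted patient factor is:

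bias = (difference in outcome by the factor) × (difference in the factor's prevalence between high- and low-climate services, given the covariates already in the model)

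The document gives neither input. With assumed values:

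| Prevalence gap | Outcome difference | Bias |
|---|---|---|
| 0 | any | 0 |
| 10 points | 20 points | 0.10 × 20 = 2 points |
| 20 points | 30 points | 0.20 × 30 = 6 points |

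The range runs from nothing to an amount that would matter. The prevalence gap must be taken conditional on type of service and the other listed covariates, which will probably make it smaller than the crude gap.

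**The case against.** Four arguments against the point deserve an answer.

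**The model is not bare.** A reader might infer that it controls only for age and gender. That is true at patient level only. Practice size, type of service and QI participation are also in it, and type of service probably takes up part of the ethnicity mix. This stands, and it limits how much confounding by ethnicity can remain.

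**Confounding is not shown.** A reader might infer that the service-level effects are confounded by case-mix. That would require the omitted variables to be associated with team climate or job satisfaction after the listed adjustments, and the document is silent on this. Type of service is a control here, so a coefficient that mixes service and patients does not by itself bias the two named exposures. This also stands: the confounding is possible, not established.

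**The article is condensed.** It does not say that this is the only analysis or that the three variables are excluded, and a fuller plan could give them a role. This stands only in part. The article goes beyond leaving detail open: it states an aim, lists the variables obtained for it, and then fixes a covariate list that does not serve that aim.

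**Baseline performance.** A reader might add that omitting the baseline outcome is an error. Baseline data exist, since Study 1 models "time (baseline, 12 and 24 month) as categorical data where baseline is set as reference". Baseline status also mattered in the trial, where the intervention was strongly associated with improvement in the "sub-group at high CVD risk that was not prescribed with recommended medicines at baseline". But nothing in Study 2 promises baseline adjustment, so nothing is contradicted. Such adjustment also changes the question from correlates of outcome to correlates of change. If team climate already shaped baseline performance, adjusting could remove part of the association being sought. It is a trade-off, not a correction.

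**Conclusion.** The mismatch is real and rests on the text alone. Study 2 seeks patient-level correlates and obtains five patient variables, and its one stated model includes two of them. That model yields no estimate for ethnicity, history of CVD or diabetes.

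A second, weaker consequence is that the team climate and job satisfaction estimates may carry residual case-mix confounding. Its size is unknown. The illustration of 0 to 6 points rests wholly on assumed prevalence gaps and outcome differences, for one factor at a time on a linear scale. It should not be set against the trial's 10-point screening effect as though it concerned the same outcome. The document supports *may be confounded* and no more.

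The point merits a change because following the stated list answers the study's own question less well than the data allow. It does not threaten the trial's results.

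**What to change.** In Study 2, Analysis, add ethnicity, history of CVD and diabetes as patient-level terms in the multilevel model, beside age and gender and with the service variables unchanged. Report their coefficients as part of the patient-level aim. If any of the three is deliberately left out, say so and give the reason.

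The cost is one sentence in the plan and three more terms. No new data are needed, since the Methods already obtain all five variables from the audit tool. The trial data cover 38,725 people in 60 services, about 645 per service (38,725 / 60), so extra patient-level terms are affordable if Study 2 uses the same data. The prescribing outcome uses only the high-risk subset, whose number the document does not give. The Trial status section says that quantitative analysis had not started, so the change can still be made in advance.

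Optionally, name a sensitivity analysis that also adjusts for baseline performance, labelled as addressing correlates of change.

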#### Methods

At the end of study follow-up visit for the TORPEDO study, all 60 health services have the option to either continue the use of the intervention or have the intervention implemented for use in the usual care health services for an additional 12 months. A post-trial clinical audit data extraction at minimum of 24 months from baseline will be conducted for the health services expressing interest to use the intervention. The objective of this study is to assess the impact of the use of the intervention over time on the two primary outcomes: (1) proportion of CVD risk factor screening and (2) proportion of appropriate medication prescription in the high risk individuals for the intervention arm and usual care arm at post-end of study following baseline.

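### Study 2 models screening and prescribing but is to be read as showing what drives use of the tool, which its described model does not measure

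*Protocol article*

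**What the plan says.** All references are to the protocol article.

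- **Reason for the evaluation** (Background, TORPEDO study): "it remains unclear how this intervention was actually used in practice and what factors promoted and hindered its use". The same section says providers could use the point-of-care tool in routine consultations, so being allocated the tool is not the same as using it.
- **Study 2, Aim:** "To determine what patient and health service level variables correlate with the trial outcomes".
- **Study 2, Methods:** the surveys go to staff at all 60 sites, so both arms are included.
- **Study 2, Analysis:** a multilevel regression is to "evaluate the influence of team climate and job satisfaction on the primary study outcomes", with patient age and gender, practice size, service type and quality-improvement participation as covariates. The results, read through the three theoretical perspectives, are to clarify which health service factors, if any, are "important drivers of use of the intervention in routine practice".
- **Primary outcomes** (Study 1, Methods): "1) proportion of CVD risk factor screening" and "2) proportion of appropriate medication prescription in the high risk individuals".
- **Study 1, Analysis:** exposure enters as intervention yes or no, crossed with time.
- **Study 1, Methods:** at the end of the trial "all 60 health services have the option to either continue the use of the intervention" or, for usual-care services, to have it installed. The later audit extraction covers the services that express interest.
- **Study 3:** interviews ask why and how staff used the tool, and video recordings show how general practitioners used it. Nine services are sampled (six intervention, three usual care).

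**The concern.** The aim and the model of Study 2 agree: both concern correlates of performance. The interpretive sentence moves to a different quantity, use of the tool. Screening and prescribing vary between services for many reasons that have nothing to do with the tool. A service with good teamwork may screen more patients without ever opening it. Conversely, a factor may strongly affect use yet leave little trace in screening, because use is only one contributor to screening and, during the trial, exists in one arm only.

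Objective 2 is to identify barriers and enablers, and the results are meant to guide translation and dissemination. If correlates of performance are reported as drivers of use, that effort could be aimed at the wrong features of health services.

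**Working it through.** The article gives no sample size, power or effect figure for Study 2, so there is no stated figure to reproduce. The main check is textual. A small illustration then shows which way the errors go.

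**1. What each quantitative study contains**

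| Study | Outcome | Exposure or predictors | Use measured? |
|---|---|---|---|
| 1 | Screening, prescribing | Intervention yes/no, time, interaction | No. The yes/no term is at most availability |
| 2 | Screening, prescribing | Team climate, job satisfaction, five covariates | None described. Trial arm is not listed either |
| 4 | Costs | Audit data, surveys, interviews | None named |

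In usual-care services the tool was offered only after the trial, so no correlate of their trial-period screening or prescribing can reflect use of it.

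**2. Inputs to the illustration**

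- From the article: 60 services; 38,725 / 60 = 645 patients per service; a 10-point absolute and 25% relative gain, which implies control screening of 0.10 / 0.25 = 40%.
- Assumed: 30 services per arm; between-service SD of 10 points; use present only in the intervention arm, averaging 0.5 with SD 0.2 at a given climate score; full use worth 20 points of screening, so average use gives 0.5 × 20 = 10 points.
- Model: service-level screening regressed on arm and a standardised climate score; 2,000 replicates.

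**3. Expected climate coefficient**

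- *Direct path, no link to use:* 3, 5 or 7 points per SD, the same in both arms.
- *Path only through use:* climate shifts use by 0.1 or 0.2 per SD (correlation with use about 0.44 or 0.70). The slope is 20 × 0.1 = 2 or 20 × 0.2 = 4 points in intervention services and 0 in usual care. The pooled slope is half of that, 1 or 2 points. The simulated means were 1.0 and 1.9, the second slightly lower because use is capped between 0 and 1.

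**4. How often the climate coefficient reaches p < 0.05**

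| Scenario | Significant |
|---|---|
| No link to anything | 5% |
| No link to use; direct 3 / 5 / 7 points per SD | 58% / 93% / over 99% |
| Acts only through use; correlation 0.44 / 0.70 | 11% / 26% |

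Hand check. The residual variance is about 0.10² + ½ × (0.20 × 0.2)² + 0.245/645 = 0.0100 + 0.0008 + 0.0004 = 0.0112, so the SD is 0.106 and the standard error about 0.106/√57 = 0.014. With a critical t of 2.00, a 3-point slope gives 0.030/0.014 = 2.14 and power of about 56%. A 1-point slope gives 0.71 and about 10%. Both agree with the simulation.

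**5. What a factor-by-arm term would add**

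On the direct path the slopes are equal in the two arms, so the expected interaction is 0. On the use path they differ by 2 or 4 points. The interaction therefore separates general performance from response to the intervention. It still does not measure use: two services can use the tool equally and gain differently from it.

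**The case against.** The strongest reply is that this is one loosely worded clause. The Study 2 aim speaks only of correlates of outcomes. The interpretation is hedged and theory-guided. The design is explanatory sequential, with qualitative data explaining the quantitative results, and Study 3 examines use directly. Objective 2 does not require a quantitative measure of use.

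Much of this stands, and it limits the point to what Study 2 can conclude. It does not remove it. Theory and nine case studies can help explain a coefficient, but they cannot turn a correlate of screening across 60 services into evidence about use. Nor is this a detail left to an analysis plan, because the article states both the outcome and the inference.

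A reader might infer several stronger things that the article does not support:

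- *That use is not studied, or that no use measure exists.* Study 3 studies it. The Logic model section lists adoption and implementation fidelity as dimensions, and its figure is not shown, so a metric may exist elsewhere. None is tied to Study 2.
- *That no change to the model helps.* A factor-by-arm term would remove much of the false-driver risk.
- *That the post-trial choice is a direct and already known measure of use.* It records adoption or willingness, comes before any exposure in usual-care services, and no result for it is reported.
- *That modelling uptake would be more powerful.* Within an assumed 30 services, power at a correlation of 0.4 is about 60% for a continuous measure and about 40% for a 50:50 decision. No advantage over the existing model is claimed.
- *That conclusions on "which intervention components promoted or had minimal impact at the provider, patient, and system levels" could rest only on staff report.* Study 3 also has video recordings and patient interviews.

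**Conclusion.** The point holds in a limited form. As described, Study 2 can identify correlates of screening and prescribing. It cannot identify drivers of use, because no use measure is described in it and its usual-care services had no tool during the trial. The inference can fail in both directions: a marker of general quality may be called a driver, and a true driver may go undetected.

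The mismatch rests on the text alone. The percentages rest on the assumed arm sizes, between-service SD and effect sizes, and on a model that includes arm but no interaction, so they show direction and plausibility and are not estimates for this trial. The false-driver risk would be smaller if an unseen analysis plan already specifies a factor-by-arm term. The matter should be settled before analysis. It concerns what one study may conclude and does not invalidate the evaluation.

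**What to change.** 1. **Limit the conclusion.** Describe the Study 2 results as correlates of screening and prescribing performance. If the model is to speak to response to the intervention, include trial arm and a factor-by-arm interaction for team climate and job satisfaction.
2. **Reserve claims about drivers of use** for Study 3 (interviews and video) and for any analysis whose outcome is use or adoption.
3. **Add a small exploratory service-level analysis of post-trial uptake,** continued or taken up versus declined. Report it by randomised arm, since continuing and starting are different decisions, and label it as adoption, not as use during the trial. If tool or portal activity is logged per service, analyse those counts in intervention services as the use outcome.

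The cost is a few lines of analysis plan and one extra analysis, provided each service's decision is recorded. The Trial status section says quantitative analysis has not begun, so the change can still be prespecified. The drawback is few services per arm: one or two predictors per model, best handled by penalised logistic regression, and wide intervals.
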